### Intervention

#### Procedures and data collection

A participant (termed “client” within the program), regardless of allocation, will receive a visit in their home from two volunteers at the start of the study and again 6 months later. The volunteers will collect data using structured surveys on the Health TAPESTRY web-based application (TAP-App) covering a variety of domains (i.e., physical activity, nutrition, mobility, quality of life; see Table 2). The volunteers will enter all data into the TAP-App using a tablet computer. The volunteers may return to the client’s home multiple times until all the surveys are complete. Participants may withdraw from the study at any point by informing the volunteer coordinator.

**Table 2 Tab2:** List of all TAP-App surveys

Construct *Survey name*	Survey description	Key information for TAP-Report	Intervention		Control	
			T_**0**_	T_**6**_	T_**0**_	T_**6**_
Demographic information *Custom*	Basic demographics	NA	X		X	
Quality of life* *EQ 5D-5L* [37]	Quality of life with respect to mobility, self-care, usual activities, pain, and anxiety/depression. Five answer options provided from able to/none to extremely difficult/extreme levels (scores ranges 0–1, higher scores = higher quality of life)	• Severe problems in walking about or unable to walk about • Severe problems washing or dressing self or unable to wash or dress self • Severe problems doing usual activities or unable to do usual activities • Severe pain/discomfort or extreme pain/discomfort • Severely anxious/depressed or extremely anxious/depressed	X	X	X	X
Physical activity *I**nternational Physical Activity Questionnaire (IPAQ)* *(short)* [38]*	Time spent doing physical activity per week	Calculated time in moderate and vigorous physical activity Time spent sitting in one typical day (in hours)	X	X	X	X
*Rapid Assessment of Physical Activity (RAPA)* [39]	Quick assessment of physical activity for older adults (score range 1–7, higher scores = higher physical activity)	Suboptimal physical activity (score < 6)	X	X	X	X
Enablement* *Patient Enablement Instrument (PEI)* [40]	Client’s ability to cope with, or have Control over their health after visit with health care team	NA	X	X	X	X
Treatment burden* *Multimorbidity Treatment Burden Questionnaire (MTBQ)* [41]	Level of difficulty of 10 treatment tasks (e.g., taking many medications)	NA	X	X	X	X
Disease burden* *Disease Burden Morbidity Assessment* (*DBMA*)[42]	Level of limitation chronic diseases have on client’s daily activities	NA	X	X	X	X
Daily life activities *Custom*	Description of client’s daily activities, any need of assistance and general thoughts about current activities	Full text responses included	X			X
Goals *Custom*	General life or health based goals	Goals listed	X	X^+^		X
Social life *Friendship Scale/Custom* [43]***	Client’s relationships with others Added questions about social life (score range 0–24, lower score = higher risk)	• Social isolation risk score (score < 15) • Felt isolated from other people most of the time (or almost always) • Felt alone and friendless most of the time (or almost always) • Transportation challenges • Loss of a partner • Living alone • Finding it hard to make ends meet	X	X		X
General health *Edmonton Frail Scale* [44]***	Falls, need of assistance with self-care and household activities, mood, medications, weight, incontinence, fall risk (score range 0–15, higher score = more frail)	• Edmonton Frail Scale score indicated high risk (score 4-15) • Uses 5+ prescription medications • Often feels sad or depressed • Sometimes loses control of bladder • More than 20 s on timed up-and-go • Requires assistance for timed up-and-go • Has fallen in last year	X	X		X
Nutrition *Screen II (8-item)* [45]	Indicates if client has a nutritional problem or at risk of developing one (score range 0–64, lower score = higher nutritional risk)	• High nutritional risk score (score < 38) • Does not know own weight or if weight changed OR lost more than 10 pounds in the past 6 months OR gained more than 10 pounds in the past 6 months • Skips meals almost every day • Poor appetite • Sometimes/often/always coughs, chokes, or has pain when swallowing food or fluids	X	X		X
Mobility [46]	Level of mobility limitations	• Preclinical or minor or major limitation in walking 0.5 km • Preclinical or minor or major limitation in walking 2.0 km • Preclinical or minor or major limitation in climbing stairs	X	X		X
Sleep *15-D* (sleep item) [47]	Sleeping difficulties	• Great problems with sleep • Severe problems with sleep	X	X		X
Personal health record *Custom*	Interest in creating a personal health record	NA	X	X^+^		X
Social context *Custom)*	Description of client’s context	Descriptive response included	X			X
Memory *Custom*	Memory difficulties	Problems with memory impact daily activities	X			X
Advance care planning *Custom*	Client’s interest in discussing advance care planning with physician	Interested in having a discussion with family physician about advance care planning	X			X
Oral health¶ *Recommended Oral Health Screening Questions* [48]	Oral health	• Problems or pain with dentures • Oral hygiene risk • Has diet risk factor for poor oral health • Family history of tooth decay • Acid reflux • Oral dryness • Symptoms of active dental disease	X		X	
Smoking and alcohol^¥^ *Custom*	Smoking and alcohol behaviors	• Wants help to address smoking behavior OR wants help to address smoking behavior in the future OR does not want help to address smoking behavior • Wants help to address drinking behavior OR wants help to address drinking behavior in the future OR does not want help to address drinking behavior	X			
Health TAPESTRY experience* *Custom*	Feedback on, and impact of Health TAPESTRY program including negative effects	NA		X		
Community program and service use *Community Programs and Services* (adapted) [49]	Community program and services connected to through Health TAPESTRY	NA		X		

*NA* not applicable

*Survey is used as a research outcome measure

¶Survey only used at Hamilton FHT site

^¥^Survey only used at Dufferin Area FHT site

^+^Follow-up survey to previous responses

#### Intervention group

For the intervention group, once all baseline surveys are completed, the TAP-App will create a summary TAP-Report from the information provided. This summary includes the client’s reported goals, key information associated with their answers and/or specific survey scores (Table 2), and volunteer observations. The TAP-Report will be reviewed by a volunteer coordinator and then securely sent using the TAP-App to the TAP-Huddle at the client’s clinic. The TAP-Huddle is an interprofessional team of health care providers who meet approximately weekly. Each TAP-Huddle is responsible for reviewing the report and creating and implementing a plan of care for each intervention client based on this review. The plan of care can involve a number of actions including a clinic visit, telephone call with a health care provider, further assessment, sharing information about or a referral to community resources. The TAP-Huddle can deliver the plan of care themselves and/or request a volunteer to help (e.g., help clients sign up for a community program). The TAP-Huddle can share a patient-friendly report (in plain language) with the client containing the patient’s goals, open-ended responses, and next steps suggested by the TAP-Huddle. At the end of the 6 months, the Health TAPESTRY volunteers will complete another visit with clients to complete the surveys for a second time.

#### Control group

Once the baseline visit is complete, control clients will receive usual care. No report will go to the TAP-Huddle until the client received the intervention, nor will any volunteer follow-up take place. After, 6-month research outcomes are collected, and clients will be offered the Health TAPESTRY program.

#### Volunteers

To manage the incorporation of trained volunteers into the program across sites, we formed a partnership with the Canadian Red Cross and the Windsor Essex Compassion Care Community to recruit, train, manage, and retain the community volunteers. All volunteers will undergo a screening process. Volunteers meeting screening criteria will receive a blended-model training program of online and in-person training specific to the Health TAPESTRY program. A full description of the volunteer program has been published elsewhere [50].

### Strategies to improve adherence to protocol

The Health TAPESTRY research team will continually monitor study participant recruitment and timelines. Bi-weekly meetings with the study team and volunteer coordinators will be held to ensure fidelity to the trial protocol and huddle process. Volunteer coordinators will provide general oversight for the TAP-Reports and address any issues volunteers may experience related to the visits. Continuing education opportunities for volunteers will be provided to clarify procedures, refresh information from initial training, and provide new information as knowledge and self-efficacy gaps become apparent. Deviations from the protocol will be documented in meeting minutes.

### Data collection

Outcome data collection will occur through the structured surveys via the TAP-App, from the electronic medical record (EMR), program records, and focus groups/interviews (Table 3). Health care utilization outcomes will be measured during the 6-month period prior to study enrollment (i.e., before baseline) and during the 6-month study period. For the EMR data extraction, all researchers will undergo training and use a standardized data abstraction form that has been pilot tested. We will calculate agreement scores between auditors for a subset of the sample.

**Table 3 Tab3:** Summary of outcomes, measures, and analysis plan using the RE-AIM framework

RE-AIM element	Outcome	Outcome measure; *source*	Data collection time point	Analysis
Reach *The reach of the intervention into the target population*	Participants	Proportion of eligible patients who consent; *self-report*	T_0_	Simple proportions and range across sites
	Sample characteristics	Demographics including chronic conditions; *self-report*, *EMR*	T_0_	Simple proportions and range across sites
	Volunteer visits	Number of volunteer visits; *program records*	T_6_	Frequency count across sites
Effectiveness *Positive and adverse effects of the intervention*	Hospitalizations*	Number of hospitalizations; *EMR*	T_0_, T_6_	Poisson regression or negative binomial regression
	Physical activity*	Total minutes spent doing moderate, vigorous, activity and walking (IPAQ); *self-report*;	T_0_, T_6_	Multiple linear regression
	Sitting	Hours sitting (IPAQ); *self-report*	T_0_, T_6_	
	Patient enablement	PEI; *self-report*	T_0_, T_6_	
	Quality of life	EQ 5D-5L; *self-report*	T_0_, T_6_	
	Treatment burden	MTBQ; *self-report*	T_0_, T_6_	
	Disease burden	DBMA; *self-report*	T_0_, T_6_	
	Emergency room or urgent care	Number of emergency room or urgent care visits; *EMR*	T_0_, T_6_	Poisson regression or negative binomial regression Poisson regression or negative binomial regression
	Falls	Number of falls; *EMR*	T_0_, T_6_	
	Medications	Number of medications; *EMR*	T_0_, T_6_	
	Primary care visits	Number of primary care visits; *EMR*	T_0_, T_6_	
	Negative effects	Unmet expectations; *self-report*	T_6_	Descriptive analysis across sites
		Labeling effect of screening tools; *self-report*	T_6_	
		Number and nature of serious adverse events; *EMR*	T_6_	
Adoption *Representation of settings and intervention agents who are willing to initiate and actively participate in program*		Number of health care providers who consent to participate; *program records*	T_6_	Simple proportions across sites
		Proportion of health care team members participating by health care profession; *program records*	T_6_	Simple proportions across sites, across professions
		NoMAD tool^£^ (NPT traffic light process); *program records*	T_1_, T_2_, T_3_, T_6_, T_9_, T_12_	Descriptive analysis across sites
		Number of volunteers recruited, trained, active, dropouts: *program records*	T_6_	Simple proportions across sites
Implementation *Fidelity to the intervention and adaptations*	Consistency of delivery as intended	Number of home visits, reports sent to clinic, number and nature of actions from TAP-Huddle; *EMR* Fidelity checklist; *program records*	T_6_	Frequencies and/or proportions across sites where appropriate
	Cost effectiveness	Program costs; *program records* QALYs; *self-report*	T_6_	Economic evaluation
	Barriers and facilitators or adaptations of implementation	*Focus groups/interviews**, program records*	T_6_ – T_12_	Descriptive thematic analysis
Maintenance *Extent to which program becomes sustained over time*	Extent that program becomes institutionalized, part of practice or policies created	Proportion of patients and team members who recommend program;* self-report*	T_6_	Simple proportions across sites
		Indication of sites continuing program; *program records*	T_12_	Frequency count across sites
		NoMAD survey^£^; *self-report*	T_12_	Descriptive analysis across sites

*EMR* electronic medical record, *NPT* Normalization Process Theory, *QALY* quality-adjusted life year, *T*_*0*_ baseline, *T*_*6*_ 6-month data collection time point, *T*_*12*_ 12-month data collection time point

*Primary outcomes for the study

^£^Based on Normalization Process Theory

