We plan to carry out this study through FHTs, so if results are reproduced, implementation studies will be needed in other settings. Patients rostered to FHTs have access to diverse health care providers, whereas patients in other models of primary care practice may not have the same level of access. However, we anticipate the results will be generalizable to other FHTs in the Ontario health care system—approximately one quarter of attached patients in Ontario are rostered to a FHT [77]—and potentially generalizable to other primary care organizations that include team-based interprofessional care and other funding models. The FHTs participating in the study are from communities across Ontario, including both urban and rural locations, and they offer a variety of clinical programs and interprofessional to patients, creating a diverse sample of sites.

A strength of this evaluation is the inclusion of outcomes to assess possible negative outcomes associated with Health TAPESTRY, including disease burden, treatment burden, and the labeling effects of screening tools. Understanding not only the benefits of Health TAPESTRY but also the risks is important prior to spread or scale. This evaluation also includes several outcomes from the first trial so as to help to elucidate findings that were close to significant, such as falls. Another strength of the proposed study is that it will test reproducibility of results from a single site RCT in multiple diverse sites, as well as evaluate implementation. Many health care innovations are developed and found to be effective, yet are not sustained as part of routine care. This may be explained by a lack of evaluating the innovations described. Another strength is the evaluation of contributing factors to implementation (barriers and facilitators) that can be compared across sites. This will provide further insight into strategies to enhance implementation in the future and the potential need for adaptations of the intervention to address contextual factors (e.g., rural/urban, primary care team make up, local volunteer capacity). Our evaluation plan that addresses both effectiveness and implementation lessons, as well as other components of RE-AIM, will provide a solid foundation to guide the scaling of Health TAPESTRY to other communities and primary health care contexts in the future.

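### Falls are counted from the medical record, but only the intervention arm has a falls answer sent to the clinic and extra contacts at which falls can be charted

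*Protocol article*

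**What the plan says.** - **Outcome and source.** Table 3 (Data collection) lists falls under Effectiveness as "Number of falls; *EMR", at baseline (T0) and 6 months (T6). Data analysis plans a Poisson or negative binomial model with an incidence rate ratio, adjusted for baseline value and site. Secondary outcomes are declared exploratory, with no alpha adjustment.
- **Who is asked about falls, and when.** Table 2 (Procedures and data collection) describes the Edmonton Frail Scale as covering "Falls, need of assistance with self-care and household activities" among other items. It is marked for the intervention arm at T0 and T6, and for controls at T6 only.
- **What reaches the clinic.** The key information that Table 2 lists for the report from this survey includes "Has fallen in last year". Under Intervention group, the report is reviewed by a coordinator, "then securely sent using the TAP-App to the TAP-Huddle", and followed by a plan of care that may include a clinic visit, a telephone call or further assessment.
- **What happens in controls.** Under Control group: "No report will go to the TAP-Huddle until the client received the intervention, nor will any volunteer follow-up take place".
- **Traces in the record.** Table 3 (Implementation) names the medical record as a source for "Number of home visits, reports sent to clinic, number and nature of actions from TAP-Huddle".
- **Why falls are included.** The Discussion says outcomes carried over from the first trial should "help to elucidate findings that were close to significant, such as falls".

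**The concern.** A rate ratio built from chart entries compares two things at once: how often participants fall, and how often a fall gets written down. The two can be separated only if recording is the same in both arms. Here the intervention acts directly on recording, by two routes:

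1. **The report.** A fall before enrollment, disclosed to a volunteer at T0, is passed to the clinic after enrollment. If it is charted, it may be counted in the study period or in the pre-enrollment period, and this can happen in the intervention arm only.
2. **The contacts.** Visits, calls and assessments started by the clinic team are extra occasions on which a new fall can be mentioned and charted. The Background reports that primary care visits rose in the first trial.

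Both routes push the ratio upward, against the program. A real reduction could disappear or appear as an excess, for an outcome that the protocol singles out as needing clarification.

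**Working it through.** The article states no falls rate and no recording rate, so there is no figure of the plan's to reproduce. The check has two parts.

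**Part 1. The arms side by side, T0 to T6**

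| Step | Intervention | Control | Source |
|---|---|---|---|
| Falls question at T0 | Yes | No | Table 2 |
| Falls answer sent to the clinic | Yes | No | Table 2; Intervention group; Control group |
| Contacts started by the clinic team | Possible | None | Intervention group; Control group |
| Falls question at T6 | Yes | Yes | Table 2 |
| Falls counted from the medical record | Yes | Yes | Table 3 |

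The first three rows differ by allocation, and all three can add chart entries. The stated safeguards are abstractor training, a pilot-tested standard form and agreement between auditors (Data collection). They make the reading of charts consistent but do not change what was written in them. Adjustment for the baseline count cannot remove a difference in recording that starts after randomization.

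**Part 2. What a difference in recording would do**

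Observed rate ratio = true rate ratio × R, where R = (share of falls recorded, intervention) / (share recorded, control).

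R is an assumption, varied from 1.0 (no difference) to 2.0. The last column is the chance that, with no true effect, the trial shows a significant excess of falls in the intervention arm. It assumes:

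- 244 per arm (488 / 2, from Sample size);
- a two-sided 0.05 Wald test on the log rate ratio with Poisson counts;
- λ = 0.1 to 0.3 recorded falls per control participant in 6 months (assumed).

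SE = √[1/(244λ) + 1/(244λR)], and chance = Φ(ln R / SE − 1.96).

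| R | Observed if true = 1.00 | Observed if true = 0.80 | Chance of a spurious significant excess |
|---|---|---|---|
| 1.00 | 1.00 | 0.80 | 2.5% |
| 1.10 | 1.10 | 0.88 | 5.3–8.5% |
| 1.25 | 1.25 | 1.00 | 12.7–29.6% |
| 1.50 | 1.50 | 1.20 | 34.1–76.6% |
| 2.00 | 2.00 | 1.60 | 79.8–99.8% |

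Worked case, λ = 0.2 and R = 1.25: expected counts are 48.8 and 61.0; SE = √(1/48.8 + 1/61.0) = 0.192; ln 1.25 = 0.223; 0.223/0.192 = 1.16; Φ(1.16 − 1.96) = 21.2%.

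Overdispersed counts would widen the SE and lower the last column. They would not change the observed ratios.

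**The case against.** **The size is unknown.** The article gives no recording share for either arm, so a reader might infer from the table that falls have been shown to be over-recorded by a given amount. They have not. The design supports an expected direction; every R above 1 is an assumption. This objection stands.

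**The report route depends on the abstraction form.** The flag is yes/no, covers a year, and carries no date or number. Table 3 says that reports sent and team actions are found in the medical record, not that the report's content is charted. A form that dates falls by occurrence would block much of this route. An article commonly leaves such rules to the full protocol, so miscounting, including distortion of the baseline count, is a possibility and not a demonstrated error. The contacts route does not depend on the form: no abstraction rule recovers a control-arm fall that was never charted.

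**Falls are secondary and exploratory, and the bias runs against the program.** Both are true, so a false claim of benefit is not the risk. The risk is a missed benefit or an apparent harm. The Discussion concedes missing chart data, but not that it may differ by arm.

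**Hospitalizations and emergency visits.** A reader might extend the argument to these, including the co-primary outcome, since they are also taken from the record. The documents do not support that. No item in Table 2 flags such events for the report, and nothing shows that a clinic team contact changes whether an admission reaches the chart.

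**Conclusion.** The point holds for falls. Recording depends on allocation by design: the same program that is being tested asks about falls, reports the answer to the clinic and creates contacts, in one arm only, during the period in which charted falls are counted. The expected direction is a higher ratio for the intervention arm. The size cannot be derived from the article. On the assumed values, R = 1.25 is enough to cancel a true 20% reduction.

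The conclusion rests on two readings: that falls use the same 6-month windows that Data collection gives for health care utilization, and that at least some team contacts lead to falls being noted. It concerns the interpretation of one secondary outcome and leaves the co-primary results untouched.

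**What to change.** 1. **Dating and source rule.** Count charted falls by date of occurrence within each 6-month window, in both arms, and do not count a fall known only from a program report. This removes the most direct one-arm artefact. Cost: a date field and a source field on the abstraction form.
2. **A check that does not depend on charting.** Add a 6-month recall question on falls to the Edmonton Frail Scale visit already held at T6 in both arms, asked of every participant. Report the between-arm comparison, adjusted for site, beside the chart count. Cost: one question at an existing visit. Recruitment began in March 2018, so some T6 visits have probably passed, and the question would cover only those still to come.
3. **Interpretation.** State in advance that the chart-based falls ratio is subject to differential recording, and read it together with the recall comparison.

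The recall question has its own weaknesses. It is self-reported to volunteers who are not blinded, intervention participants have already been asked about falls at T0, and controls have no baseline value. It should therefore stand beside the chart count and not replace it. Nor should all entries from team-initiated contacts be excluded: that would delete genuine falls in the intervention arm only and bias the ratio toward benefit.
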